## Abstract

Colorectal Carcinoma (CRC) ranks among the most prevalent cancers globally, with significant variability in incidence rates across different regions. A shift towards a Westernized diet has been implicated in rising cancer rates, particularly in emerging nations. By 2020, CRC is projected to represent a notable proportion of global cancer cases and deaths. In India, CRC primarily affects individuals aged 45 to 84, with a higher incidence in males, commonly occurring in the rectum and sigmoid colon. Risk factors such as obesity, dietary factors, sedentary lifestyle, smoking, and alcohol use contribute to CRC development, especially in aging populations. Diagnosis involves various imaging modalities and histological assessments using Tumour, node and metastasis (TNM) and American Joint Committee on Cancer classifications. Recent advancements in targeted therapies like monoclonal antibodies against HER2 have shown promise in treating metastatic CRC. Immunohistochemistry markers like Ki-67 and HER2 play crucial roles in prognostic assessment and treatment planning. This study aims to investigate Ki-67 and HER2 expression in CRC, correlating with histological characteristics and prognostic factors.

## Introduction

Colorectal carcinoma (CRC) is one of the most prevalent malignancies globally, and it is the fourth leading cause of cancer-related death. CRC incidence rates vary greatly, with roughly 60% of cases identified in wealthy nations. The switch to a more Western diet has been linked to an increase in cancer rates in emerging nations [1]. In 2020, CRC will account for 10% of global cancer incidence and 9.4% of cancer-related deaths, trailing only lung cancer, which will account for 18% of fatalities. According to projections of population growth, ageing, and human progress, the global number of newly diagnosed CRC cases is predicted to reach 3.2 million by 2040.Based on projections of ageing, population expansion, and human progress, the worldwide number of new CRC cases is expected to reach 3.2 million by 2040 [2]. The majority of Indian research show that these tumours occur in people aged 45 to 84, with a male preponderance. The most likely locations for carcinomas are the rectum and sigmoid colon. Carcinoma is a malignant neoplasm of epithelial origin or a cancer originating from internal and external lining of the body. All cancers of the large intestine (colorectal cancer) originate from the cecum to the anus. Colon cancer, which extends from the cecum to the sigmoid (about 15 cm above the anal margin), and rectal cancer, which extends from the recto-sigmoid to the anus, are the two types of colorectal cancer. CRC originates as a benign polyp on the inner lining of the colon or rectum [3]. Unfavorable stressors like obesity, calorie rich diet, and diet devoid of fibre, minimal physical activity, cigarette smoking, and alcohol consumption, in addition to an ageing population in high-income nations, epithelial cells are exposed for a lengthened transit time. As a consequence, colorectal epithelium will be more susceptible to the impact of mutagenic compounds, thereby increasing cancer risk [4]. Patients may have a variety of signs and symptoms, including occult overt rectal bleeding, bowel changes, anaemia, or abdominal discomfort. Individuals over the age of 45 should have a colonoscopy if they experience rectal bleeding. CT colonography or MRI abdomen and pelvis are complimentary imaging methods for the diagnosis of colorectal cancer. MRI is used to do locoregional staging in rectal cancer. PET-CT imaging is also being used. The Tumour, node and metastasis (TNM) and American Joint Committee on Cancer classifications are used to predict the prognosis of newly diagnosed colorectal cancer (CRC) (8^th^ edition). Tumor extent, lymph node status, tumour grade, and lymphatic and venous invasion evaluation remain the major morphological prognostic variables. Tumor budding and tumour border configuration are crucial additional histological markers, however they are not considered critical in prognosis [5]. The availability of monoclonal antibodies against the vascular endothelial - and epidermal growth factor receptor has recently boosted the therapeutic arsenal. In mCRC, preclinical and clinical trials of Anti-HER2 targeted therapy have shown promising results. Because of the high mortality rate in advanced metastatic cancer, it appears that improved detection procedures are necessary. The concept of antibodies attaching selectively to antigens in biological tissues to detect antigens in cells of a tissue segment is utilized in Immunohistochemistry (IHC). The antibody-antigen binding can be seen in a variety of ways. In histology, immunohistochemistry is used to identify the presence of a particular protein marker that can help with tumour categorization and diagnosis. ErbB-2 is a receptor tyrosine-protein kinase that is also known as HER2. The prognostic biomarker human epidermal growth factor receptor 2 (HER2) is utilised to detect tumoral tissues. The transmembrane receptor protein is present on all normal cells and is involved in a wide range of biological processes such as cell proliferation and apoptosis, differentiation, and cell migration [4]. HER2 protein overexpression or gene amplification has been associated with higher stage, positive lymph node status and tendency for poor overall survival. Ki-67 as a prognostic predictor for well-known cancers. It has been established that its expression is inextricably bound to cell growth. Ki-67 expression and proliferation activity appear to rise dramatically, and it is essential in the majority of cell cycle stages. Elevated expression of Ki-67 in CRC is related with a lower survival rate, carcinogenesis, and cancer cell metastasis, suggesting that Ki-67 might be used as a prognostic biomarker in CRC patients [4]. The current study proposes to investigate the status of Ki-67 and HER2 expression in colorectal carcinomas in connection to prognostic parameters such as histological type, grade, tumour size, and lymph node status. The objectives were a) to confirm already diagnosed colorectal carcinoma by histopathological examination; b) to determine histological grades of CRC based on histopathological prognostic markers;m c) to determine staging of colorectal carcinoma by TNM classification based on American Joint Committee of Cancer (AJCC); d) to asses HER2 and Ki-67 expression in tumor tissues of colon and rectum by immunohistochemistry; e) to compare Ki-67 and HER2 expression with histopathological prognostic markers and TNM staging.

## Methods

**Review Question**: how do HER2 and Ki-67 expression levels correlate with histopathological parameters in colorectal carcinoma? What is the comparative prognostic value of HER2 and Ki-67 immunohistochemical markers versus TNM staging in colorectal carcinoma? Can HER2 and Ki-67 immunohistochemical analysis provide additional prognostic information beyond traditional histopathological parameters in colorectal carcinoma? How do HER2 and Ki-67 expression patterns vary across different stages of colorectal carcinoma according to TNM staging? What are the implications of incorporating HER2 and Ki-67 immunohistochemistry into the prognostic assessment of colorectal carcinoma alongside TNM staging and histopathological features?

**Study Design**: the current study is an observational, cross-sectional, retrospective, and prospective study that will last two years (June 2022 to June 2024), in the Histopathology and Immunohistochemistry division of the Department of Pathology, Jawaharlal Nehru Medical College, Sawangi (Meghe), in coordination with the Department of General Surgery, Acharya Vinoba Bhave Rural Hospital, Sawangi (Meghe). Approval will be obtained from Institutional Ethics Committee and informed consent will be taken from the patients participating in this study.

**Inclusion Criteria**: a) already diagnosed as colorectal carcinoma on histopathology; b) all operated cases of colorectal carcinoma; c) primary cases of colorectal carcinoma without any history of previous treatment; d) all patients with colorectal *carcinoma arising de novo*.

**Exclusion Criteria**: 1) all benign lesions of colon and rectum; b) all the already treated cases of colorectal carcinoma; c) all patients with colorectal carcinoma where the cancer is arising as a result of recurrence; d) patients with no histological confirmation of colorectal carcinoma.

**Participant's intervention comparison and outcomes (PICO)**: the information for PICOs (participants, intervention, comparison, and outcomes) is provided below;

**Population**: patients diagnosed with colorectal carcinoma (CRC).

**Intervention**: immunohistochemical analysis of HER2 and Ki-67 expression levels [6,7].

**Comparison**: comparison with histopathological parameters and TNM staging.

**Outcomes**: evaluation of the utility of HER2 and Ki-67 as prognostic markers in CRC and comparison with traditional histopathological parameters and TNM staging in predicting disease prognosis.

**Information sources**: the search will use sensitive topic-based strategies designed for each database. The search will be carried out in the following databases: Pubmed, Embase, Cinahl, Research Gate, Ajol, Google Scholar, Web of Science, Scopus and Cohrane Library. Only observational studies will be included.

**Search strategy**: ((“Colorectal Neoplasms”[MeSH] OR “Colorectal Carcinoma”[Text Word]) AND ("HER2"[MeSH] OR “HER2 Positive”[Text Word]) AND ("Ki-67 Antigen"[MeSH] OR “Ki-67”[Text Word]) AND ("Immunohistochemistry"[MeSH] OR “IHC”[Text Word]) AND ("Prognostic Markers"[MeSH] OR “Prognostic Factors”[MeSH] OR “Prognosis”[MeSH]) AND ("Histopathological Parameters"[MeSH] OR “Histopathology”[MeSH]) AND ("TNM Staging"[MeSH] OR “TNM Classification”[MeSH])).

**Sample size**: sample size calculation for a study estimating a population prevalence was described by Daniel in 1999. The calculation is intended to determine an adequate sample size to estimate the population prevalence with a good precision. The sample size calculation will be performed according to the formula suggested by Daniel.

$$\frac{{\left(Za/2\right)}^{2}*p*\left(1-p\right)}{d^{2}}$$

Where, “Z a/2” is the level of significance at 5% that is 95% confidence interval = 1.96 “p” is the prevalence of colorectal carcinoma = 0.2854 “d” is the desired error of margin = 7% = 0.07 “n” is the sample size. n = 1.96^2^x 0.2854 x (1-0.2854)/ 0.07^2^= 63.85 = Approximately 60-65 patients are needed in each study group. Study Reference: Consensus document for management of colorectal carcinoma by ICMR Formula Reference: (1999) Statistical formulas: Kappa statistics, Test statistics Software Used: SPSS 27.0 Version Level of study: Level III Sample Allocation: Random Selection of patients Study Design: Prospective Cross-sectional study.

**Approach to present study**: (Figure 1) the approach for the current study is detailed in the figure provided below. This figure outlines the step-by-step approach used in conducting the research and presenting the findings. It encompasses various stages of the study like determining the tumor staging using TNM (Table 1), Evaluation of expression of Ki-67 (Table 2) and HER2 (Table 3). This approach ensures transparency and clarity in how the study was conducted, facilitating reproducibility and reliability of the results.

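### Three of the five review questions and the stated outcome concern prognostic value, but the study is described as cross-sectional with no prognostic outcome

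*Protocol article*

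**What the plan says.** The Review Question paragraph of the Methods poses five questions. Three are about prognosis:

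- The second asks "What is the comparative prognostic value of HER2 and Ki-67 immunohistochemical markers versus TNM staging in colorectal carcinoma".
- The third asks "Can HER2 and Ki-67 immunohistochemical analysis provide additional prognostic information beyond traditional histopathological parameters in colorectal carcinoma".
- The fifth asks what follows from adding the two stains to prognostic assessment.

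The first (correlation with histopathological parameters) and the fourth (variation across TNM stages) are about association. The Outcomes item of the PICO list is "evaluation of the utility of HER2 and Ki-67 as prognostic markers in CRC and comparison with traditional histopathological parameters", and it goes on to TNM staging and the prediction of prognosis: "comparison with traditional histopathological parameters and TNM staging in predicting disease prognosis".

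On design, the Study Design paragraph says "the current study is an observational, cross-sectional, retrospective, and prospective study that will last two years". The Sample size paragraph says "Study Design: Prospective Cross-sectional study". The last of the five objectives in the Introduction is "to compare Ki-67 and HER2 expression with histopathological prognostic markers and TNM staging". The Statistical analysis paragraph in the Discussion plans a chi-square test and a multiple linear regression on factors contributing to metastasis. The Conclusion section will draw on correlation of expression with histology and TNM.

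**The concern.** Prognostic value is a statement about what later happens to the patient. To compare a marker with TNM as a predictor, or to show that it adds to TNM or histology, one needs a third variable that both are trying to predict. The article describes none. TNM and histology are the comparators, and they are also the only variables against which the markers are tested.

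What is at stake is what the study may conclude. With the outcome worded as it is, the chi-square associations with stage and grade are the main material available for judging prognostic utility. They bear on that judgement in neither direction. A marker that tracks stage closely may be redundant with it, and a marker unrelated to stage may still be prognostic.

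**Working it through.** The article gives no figure for this point, so the check sets its parts side by side.

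**1. What each question needs, and what is described.** Write X for the marker score, S for TNM stage, G for grade and other histology, and Y for a later patient outcome.

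| Question or item | Needs | Described? |
|---|---|---|
| 1. Correlation with histopathology | X with G | Yes |
| 2. Comparative prognostic value against TNM | Y given X, against Y given S | No Y |
| 3. Added information beyond histopathology | Y given X and G, against Y given G | No Y |
| 4. Variation across TNM stages | X with S | Yes |
| 5. Implications for prognostic assessment | Answers to 2 and 3 | No Y |
| Outcomes item (predicting prognosis) | Y | No Y |
| Objectives (a) to (e) | Diagnosis, G, S, X, and X with G and S | Yes |

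Three of the five questions and the only Outcomes item lack the variable they depend on. A larger sample gives a more precise joint distribution of X, G and S. That distribution is compatible with X adding nothing to S and with X adding a great deal, so sample size cannot settle the matter.

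**2. Search for a Y elsewhere in the article.** Survival appears only as background in the Introduction. The tables and the sections on grossing, staining and interpretation cover staging, marker scoring, processing and grade. The analysis names no time-to-event or predictive-performance method. The sample size formula sets the precision of a prevalence and contains no event count, effect size or follow-up time.

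**3. Could metastasis serve as Y?** With no follow-up described, metastasis can only be N or M status when the tumour is staged. By Table 1, any M1 category makes the tumour stage IV whatever T and N are, and stages 0 to III are all M0. Stages 0 to II are N0, and every stage III row is node-positive.

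- Distant metastasis is thus fixed by stage, and nodal status is fixed by stage except within stage IV.
- With TNM among the predictors, the outcome is largely or wholly contained in a predictor, and no marker can beat it or add to it.
- With TNM left out, the regression shows only that a marker goes with a component of TNM. That is the association question again.

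**4. Would adding follow-up be a realistic alternative?** This is illustration only. The hazard ratios and marker prevalences are assumptions, since the documents give none. For a two-group comparison with two-sided alpha 0.05 and 80% power, Schoenfeld's formula is

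events = (1.96 + 0.84)² / [p(1 − p)(ln HR)²], with (1.96 + 0.84)² ≈ 7.85.

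| Marker-positive share p | HR 2.0 | HR 3.0 |
|---|---|---|
| 0.50 | 7.85 / (0.25 × 0.480) → 66 | 27 |
| 0.30 | 7.85 / (0.21 × 0.480) → 78 | 31 |
| 0.10 | 7.85 / (0.09 × 0.480) → 182 | 73 |

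The Materials list gives about 60 specimens. For a hazard ratio of 2.0 the required events exceed the number of patients at each of these prevalences, and this is before any adjustment for TNM. With an assumed 20 events, power for a hazard ratio of 2.0 would be 34%, 30% and 15% respectively.

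**The case against.** **The article condenses a fuller protocol, and Figure 1 is not shown.** This stands in part. One may say that no follow-up is described, but not that none will be collected. A reader might infer the latter, and the article does not establish it. The point does not rest on an omission, however. The outcome, design, objectives and analysis are all stated, and they conflict.

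**The study is also called retrospective and prospective.** Both design statements include the word cross-sectional, and no outcome ascertainment is described. The terms fit the way cases are gathered.

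**The questions may belong to a literature review.** The Review Question and PICO headings, the database list and the search string make this a fair reading of the layout. It does not remove the conflict. The PICO intervention is the immunohistochemical analysis itself, and the only analysis planned is of the specimens.

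**Stage and grade are accepted prognostic factors.** That supports an aim of association with them. It does not support a claim of value against or beyond them, because a yardstick cannot be outperformed when it is also the standard of measurement.

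**The stated aims are already narrower.** This stands. The Abstract, objective (e) and the Conclusion speak of correlation or comparison with histology and TNM. A reader might infer that the investigators will report superiority over TNM from a significant chi-square test. No sentence says so. The fault lies in the wording of the questions and the outcome.

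**M status may come from outside the specimen.** Also true. A reader might suppose that every measurement comes from the resected bowel, but Table 1 needs M categories that a bowel specimen often cannot supply. M status is still a baseline measurement, so the reasoning does not change.

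**Conclusion.** The point holds for the second, third and fifth review questions and for the Outcomes item: three of five questions and the sole stated outcome. As described, the study has no prognostic outcome, and the metastasis regression does not supply one because metastasis at staging is part of TNM. No sample size repairs this.

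The conclusion assumes that the article's silence on follow-up reflects its cross-sectional label, and that metastasis means status at staging. If the full protocol defines follow-up and later metastasis, the cross-sectional label is what would have to be corrected.

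A reader might go further and infer that the study cannot answer its aims at all. The documents do not support that. The first and fourth questions and all five objectives can be answered with the data described.

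**What to change.** - Restate the Outcomes item and the second, third and fifth questions as the association of HER2 and Ki-67 expression with histological type, grade, tumour size, nodal status and TNM stage. This agrees with the Abstract, the Introduction and the Conclusion.
- Delete the claims of comparative value, of additional prognostic information and of predicting prognosis.
- In the Statistical analysis paragraph, say that the regression concerns metastasis at staging and is not evidence of prognostic value.
- Leave the first and fourth questions, objectives (a) to (e) and the Conclusion as they are.

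Collecting survival data from records is not recommended as a patch. The Sample size paragraph calls the study prospective, so the number of retrospective cases is unknown, and the illustration above suggests that too few events would accrue to be informative.

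The change costs a few sentences and no new data. The downside is a more modest claim.

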**Materials**: a) the study will include approximately 60 resected specimens from confirmed and planned Colectomy specimen received in the Department of General Pathology, J.N.M.C; b) formalin fixed, paraffin embedded blocks of tumor masses from resected Colectomy specimens; c) 10% formalin; d) grossing instruments (grossing tray, knife, scalpel, measuring tape, plain forceps, toothed forceps); e) automated tissue processing assembly; f) haematoxylin & Eosin stain; g) HER2 and Ki-67 marker; h) glass slides (Blue Star®). Dimensions: 7.5x 2.5 centimeters; i) binocular research microscope.

**Staining Protocol: haematoxylin and eosin staining** [9]: a) colorectal carcinoma sections are deparaffinized in xylene: Three 10-minute shifts; b) sections dewaxing is performed. Sections are rehydrated using progressively higher grades of alcohol; c) bring sections to water; d) in a jar, stain for 10 minutes with Harris hematoxylin; e) wash for 2-3 minutes under running water; f) for a few seconds, separate in 1 percent acid alcohol (1 percent HCl in 70% alcohol); g) alkaline water was used for 5 minutes; h) for 1 minute, stain in 1% aqueous Eosin; g) dehydrate through 90% alcohol; h) fount in Dibutylphthalate Polystyrene Xylene (DPX).

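### The sample size is derived from the prevalence of colorectal carcinoma in a cohort where every patient has it, so the stated 7-point precision is not derived for any study endpoint

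*Protocol article*

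**What the plan says.** The Sample size paragraph (Methods) gives the purpose of the calculation: "The calculation is intended to determine an adequate sample size to estimate the population prevalence with a good precision". It then lists the inputs. The z-value "is the level of significance at 5% that is 95% confidence interval = 1.96", p "is the prevalence of colorectal carcinoma = 0.2854", and d "is the desired error of margin = 7% = 0.07". The stated result is "63.85 = Approximately 60-65 patients are needed in each study group". The source named for p is a consensus document on the management of colorectal carcinoma.

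The first inclusion criterion is "already diagnosed as colorectal carcinoma on histopathology". The exclusion criteria remove anyone without histological confirmation, and the PICO population is patients with this diagnosis.

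The relevant objectives at the end of the Introduction are "to asses HER2 and Ki-67 expression in tumor tissues of colon and rectum by immunohistochemistry" and a comparison of the two markers with histopathological prognostic markers and TNM stage. The Statistical analysis paragraph plans a chi-square test and a regression for metastasis.

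Under Materials, "the study will include approximately 60 resected specimens".

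**The concern.** A precision formula supports a sample size only if its p is the proportion that the study will estimate. Here p is the frequency of a disease that every participant must have in order to enter. The proportions of interest are the HER2 classes and the Ki-67 expression classes among carcinomas. The protocol gives no expected value for either, and none enters the formula.

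Two things are at stake. A reader will take 7 points as the precision of the marker results, although it was not calculated for them. And nothing in the calculation bears on the marker-by-stage and marker-by-grade comparisons, so a non-significant result could be given more weight than about 60 specimens allow.

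The same paragraph has two further faults that any rewrite has to deal with: the printed inputs do not give the printed result, and the number is stated per study group although no groups are defined and Materials plans about 60 specimens in all.

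**Working it through.** **Inputs from the protocol article.** Sample size: z = 1.96, p = 0.2854, d = 0.07, stated result 63.85 (60-65 per group). Materials: about 60 specimens. No HER2 or Ki-67 proportion, effect size or power is given, so every marker proportion below is an assumption shown as a range.

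**1. The plan's own figure.** n = z²·p·(1−p)/d² = 1.96² × 0.2854 × 0.7146 / 0.07² = 3.8416 × 0.20395 / 0.0049 = 159.9. The stated 63.85 is not reproduced. Common variants also miss it: one-sided 5% z gives 112.6, an 80% interval 68.4, d = 0.14 gives 40.0, and unsquared z 81.6. With the other inputs held, 63.85 needs d of about 0.111, p of about 0.089 or z of about 1.24. At p = 0.2854 the half-width is 1.96 × √(0.20395/60) = 11.4 points with 60 patients and 11.0 with 65.

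**2. Does p match an endpoint?** Entry requires confirmed colorectal carcinoma, so its proportion in the sample is 1 by design. The estimated proportions are marker classes. The two do not correspond.

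**3. Precision for the markers at n = 60.** Half-width = 1.96 × √(p(1−p)/60). The last column is the n that would keep d = 0.07.

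| Assumed marker proportion | Half-width at n = 60 (points) | n for ±7 points |
|---|---|---|
| 5% | 5.5 | 38 |
| 10% | 7.6 | 71 |
| 20% | 10.1 | 126 |
| 30% | 11.6 | 165 |
| 50% | 12.7 | 196 |

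The normal approximation is rough when positives are few. Exact 95% limits are 1.0-13.9% for 3/60, 3.8-20.5% for 6/60 and 10.8-32.3% for 12/60.

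**4. When does ±7 points hold?** It needs p(1−p) ≤ n × 0.0049/3.8416. At n = 60 the right side is 0.0765, so p ≤ 0.084. At n = 65 it is 0.0829, so p ≤ 0.091. The margin holds only for positivity below about 8-9% (or, by symmetry, above about 91-92%).

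**5. Associations, as a guide only.** Noncentral chi-square, n = 60, two-sided 5%, 80% power, with w = √(λ/60):

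| df | λ | Detectable w |
|---|---|---|
| 1 | 7.85 | 0.36 |
| 3 | 10.90 | 0.43 |
| 6 | 13.62 | 0.48 |
| 9 | 15.65 | 0.51 |

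The df depends on how classes are collapsed. HER2 in the three classes of Table 3 by four main stages has 6 df; HER2 reduced to two classes by four stages has 3; Ki-67 in the four classes of Table 2 by four stages has 9. The article does not fix the collapsing. For HER2 the approximation itself is doubtful: 3, 6 or 12 positives spread evenly over four stages give expected counts of 0.75, 1.5 or 3 per cell, all below 5.

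**The case against.** A reader might infer that about 60 specimens are too few for everything the study sets out to do. The document does not support that. What fails is the justification, not necessarily the number. If the marker is rare, 60 specimens meet the stated margin: about 5.5 points at an assumed 5%. Precision-based sizing is also an accepted approach for a descriptive cross-sectional study.

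It can also be said that a detectable association, and wording on how to read null results, are details that an article may leave to a fuller document, and that the article nowhere commits to reading a null result as no association. Both are fair. The absence of a power calculation is therefore not the point here, and the w values are only a guide for authors who choose to quote one.

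Finally, 0.2854 might be a marker rate under the wrong label. The text does not say so. If it were, the formula would still give about 160, and 60-65 patients would still give about 11 points.

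What remains is a stated input that is the wrong quantity, which no companion document is needed to see.

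**Conclusion.** The point holds for the justification: p = 0.2854 is a disease prevalence that an all-carcinoma cohort cannot estimate, and the 7-point margin is not derived for HER2 expression, Ki-67 expression or their associations. On assumed marker proportions of 5% to 50%, the half-width with 60 specimens runs from 5.5 to 12.7 points, and 7 points is met only below about 8-9%. These figures rest on simple binomial sampling, one analysable specimen per patient and a total of 60.

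The data remain usable, so the plan should be corrected but the study is not undermined. Changing the label on p would not be enough, because the arithmetic and the per-group wording would still be wrong.

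**What to change.** Rewrite the Sample size paragraph.

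- Replace p with the expected HER2-positive proportion and, separately, the expected strongly positive Ki-67 proportion among colorectal carcinomas, each labelled as an assumption.
- Withdraw the 7-point claim. State the 95% half-width that about 60 specimens give at those proportions, with exact limits where few positives are expected.
- Correct the arithmetic: the printed inputs give 159.9, and at p = 0.2854 the planned 60-65 patients give about 11 points.
- Reconcile the per-group number with the total of about 60 specimens under Materials. Either define the groups or drop the phrase.
- If a detectable association is quoted, call it approximate, say how stage and marker classes are collapsed, and note that the chi-square approximation is unreliable for sparse HER2-positive cells. A non-significant result should not be read as excluding a moderate association.

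The cost is one paragraph, with no change in enrolment. The price is a less favourable stated precision. If the authors prefer to keep ±7 points, enrolment would have to change unless the marker is rare: 71 patients at an assumed 10%, up to 196 at 50%.

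### The sample-size formula with its own printed inputs gives 160 patients, not 63.85, so the planned 60 to 65 patients do not deliver the 7-point margin of error

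*Protocol article*

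**What the plan says.** The Sample size paragraph of the Methods sets out the aim: "The calculation is intended to determine an adequate sample size to estimate the population prevalence with a good precision". It gives the formula z² × p × (1 − p) / d² and defines each input. The multiplier "is the level of significance at 5% that is 95% confidence interval = 1.96", p "is the prevalence of colorectal carcinoma = 0.2854", and d "is the desired error of margin = 7% = 0.07". It then writes the substitution in full and gives the result: "n = 1.96^2^x 0.2854 x (1-0.2854)/ 0.07^2^= 63.85 = Approximately 60-65 patients are needed in each study group".

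The Materials paragraph of the Methods gives the operational number: "the study will include approximately 60 resected specimens from confirmed and planned Colectomy specimen". The Population and Comparison entries of the Methods describe one set of patients with colorectal carcinoma, in whom marker expression is compared with histopathology and TNM stage. The text shown defines no separate study groups.

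**The concern.** The formula, the definitions of its inputs and the substitution all agree with one another, and only the result does not follow. This line is the article's sole quantitative justification for the sample size. If the result is wrong, the one precision target in the plan is not met by the planned number, and any proportion of about this size will be reported with much wider uncertainty than the plan promises.

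The per-group wording adds a second problem. A formula for one proportion does not yield a per-group number, and the phrase conflicts with a total of about 60, so the recruitment target itself is unclear.

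**Working it through.** **Inputs**, all from the Sample size paragraph: z = 1.96, p = 0.2854, d = 0.07. The planned number is 60 to 65 there and about 60 in Materials.

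**Step 1: try to reproduce the printed figure.**

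n = z² × p × (1 − p) / d²

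- z² / d² = 3.8416 / 0.0049 = 784
- p × (1 − p) = 0.2854 × 0.7146 = 0.203947
- n = 784 × 0.203947 = **159.89, so 160**

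The printed 63.85 is not reproduced. The ratio is 159.89 / 63.85 = 2.50.

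**Step 2: look for a convention that would give 63.85.**

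| Variant | n |
|---|---|
| One-sided 5% | 112.6 |
| z not squared | 81.6 |
| Continuity correction (add 1/d) | 174.2 |
| d read as the full interval width | 639.6 |
| d read as relative to p | 1963 |

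None matches. A finite population correction would need a population of (159.89 − 1) / (159.89 / 63.85 − 1) ≈ 106, and the article mentions neither such a population nor such a correction. With the other inputs unchanged, 63.85 would require d ≈ 0.111, or p ≈ 0.089 (or its mirror, 0.911), or z ≈ 1.24, which is about 78% confidence.

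One slip fits closely. Using p in place of (1 − p) gives 784 × 0.2854² = 784 × 0.081453 = 63.859, which truncates to 63.85. This is an inference from the numbers, not something the article states, but it points to a calculation error and not to damage in the text.

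**Step 3: the margin that the planned number delivers.**

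Half-width = 1.96 × √(0.203947 / n)

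| n | 95% half-width (percentage points) |
|---|---|
| 60 | 11.4 |
| 64 | 11.1 |
| 65 | 11.0 |
| 160 | 7.0 |

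Relative to 7 points, 11.43 / 7 = 1.63 at n = 60 and 10.98 / 7 = 1.57 at n = 65. The Wilson interval gives nearly the same answer: a half-width of 11.2 points at n = 60 and 10.7 at n = 65.

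**Step 4: does the per-group reading help?** Two groups of 60 to 65 pooled would be 120 to 130 patients. The half-width is then 8.1 to 7.8 points, still above 7.

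**The case against.** The arithmetic cannot be defended. The best case on the other side is that the error does little harm. The article labels p as the prevalence of colorectal carcinoma, yet every enrolled patient already has the disease, so the study cannot estimate that quantity. The Statistical analysis paragraph plans chi-square tests and multiple linear regression, with no interval for a prevalence. On this view the 7-point margin belongs to nothing the study will report, and restating it at p = 0.2854 merely gives a correct margin for an irrelevant proportion. It can be added that nothing in the text says 60 to 65 was chosen for feasibility, that Materials already gives a total of about 60, and that Figure 1, which is not shown, might define groups.

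Part of this stands. The label on p is a separate defect, and correcting the arithmetic does not size the study for associations between the markers and stage. It is also true that keeping 60 to 65 and widening the margin is a choice that the sponsor must own. None of it makes the printed equation true. Assessing HER2 and Ki-67 expression is one of the stated objectives, and a margin stated as conditional on p = 0.2854 is valid for any proportion of that size, marker positivity included. Grouping does not rescue the figure either, as Step 4 shows.

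**Conclusion.** The concern holds. The printed formula and inputs give 160 patients, about 2.5 times the stated 63.85, and 60 to 65 patients give a 95% half-width of 11.4 to 11.0 points at p = 0.2854 instead of 7.

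The figure of 160 rests only on the article's own inputs. The achieved margin rests on p = 0.2854 and the usual normal approximation, and it changes with p. The article gives no expected marker-positivity rate. Taking illustrative values with n = 60, the half-width would be 1.96 × √(0.25 / 60) = 12.7 points at p = 0.50 and 1.96 × √(0.09 / 60) = 7.6 points at p = 0.10. The conclusion that the per-group wording is out of place rests on the text shown, which describes a single cohort.

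**What to change.** Correct the calculation in the Sample size paragraph and make it agree with Materials:

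- If the planned number is kept, state that about 60 to 65 patients in total give a 95% half-width of about 11 percentage points for a proportion of 0.2854.
- If a 7-point margin is really required, state n = 160 and change the number in Materials to match.
- In either case, delete the phrase that makes the figure a per-group requirement.

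The first option changes wording only. It needs no extra patients, and its cost is a less favourable stated precision. The second means about 100 more specimens than the 60 planned (160 − 60).
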